**Figure 1 F1:**
[figure not shown]
**Flow of patients in the randomised controlled trial of Specialist Mood Disorder Team versus usual care**.

The RCT forms part of the Nottinghamshire Derbyshire and Lincolnshire Collaboration for Leadership in Applied Health Research and Care (CLAHRC NDL), an applied health services research centre funded by the Department of Health, the University of Nottingham and nine health and social organisations in three English counties [18]. It focuses on service innovation and implementation of research as well as clinical and cost effectiveness of interventions that are perceived by the local health services to be a high priority.

Unlike traditional RCTs, which favour a small number of clinical outcomes, service delivery studies of complex interventions require multiple outcomes [19]. Service delivery studies are interested in a range of equally important outcomes including clinical outcome, cost effectiveness, access to services, burden on staff and risk of serious adverse events. Nevertheless, multiple outcome measures can lead to false positive conclusions about the effectiveness of a treatment so a primary outcome variable (change in depressive symptoms) is specified. In order to interpret the results of such a RCT, and identify important processes and context variables required for replication, a range of outcomes and process variables is necessary [19]. Therefore, alongside the RCT an implementation analysis of barriers and drivers to effective care using largely qualitative methods is performed. An audit will be performed of the standard of care delivered to the patient by secondary mental health care before and after entry to the study using NICE Guidelines for depression, the standard of care that is expected to be delivered in England and Wales [8,20]. The standard of care provided by the continuing treatment teams in the secondary care mental health services is important to measure in order to interpret the results of the RCT; if the standard of care is high in usual care, there may be ceiling effects operating even if the specialist depression disorder team is effective, but if usual care is poor then the specialist depression disorder team may be effective merely because it is providing an acceptable standard of care. In the latter case, the implication might be that better training and support for existing staff is required rather than the formation of a specialist depression disorder team.

A further audit will carried out to examine the representativeness of the sample who enter the RCT in terms of both demographic characteristics and the treatments they have received to examine the generalisability of the results. Finally, for the purposes of replication, both descriptive statistics and analytical methods using a range qualitative approaches and quantitative process measures will be employed. Unlike simple drug and psychological treatment interventions, services can vary at many levels (organisationally, clinician-patient, patient sample, nature of treatment) so it is important to specify the important constituents of an effective intervention and the processes that are necessary to achieve a successful outcome [19].

### Sample and inclusion/exclusion criteria

The intention to participants in secondary care mental health services who continue to suffer from moderate or severe depression despite continuous treatment for at least six months. Such patients may receive in addition to secondary care mental health services, interventions for depression provided by primary care, voluntary and private sectors. Eligible patients will be under the care of a secondary care community mental health team or out-patient services provided by three mental health trusts in England. The Structured Clinical Interview for DSM-IV Axis 1 Disorders [21] will be used to describe patients' symptom profile at baseline. The pragmatic nature of this study requires that inclusion/exclusion criteria must reflect everyday criteria that NHS clinicians use and would be used by a specialist depression disorders team [22]. Inclusion criteria are:

• The responsible medical officer or care coordinator leading the patient to be suffering from primary unipolar depression which is not a consequence of having another axis 1 or 2 psychiatric disorder;

• Age over 18 years;

• Able and willing to give oral and written informed consent to participate in the study;

• From the date of first assessment by a health professional working within the index mental health trust, primary care trust or third sector, they must have been offered or received direct and continuous care from one or more health professionals in the preceding 6 months. They must currently be under the care of a secondary care mental health team;

• Meets NICE criteria for moderate depression (five out of nine symptoms of depression [8]); has a Hamilton Depression Rating Scale of at least 16, indicating at least moderate severity depression [23]; and score 60 or less on the Global Assessment of Functioning Scale implying at least moderate impairment in social or occupational function and/or moderate symptoms of depression [24].

Exclusion criteria are:

• Is receiving emergency care for suicide risk, risk of severe neglect or homicide risk; however, patients will not be excluded because of such risk provided the risk is adequately contained within their current care setting and the primary medical responsibility for care remains with the referring team;

• Does not speak fluent English;

• Is pregnant

• Unipolar depression is secondary to a primary psychiatric or medical disorder.

However, patients with bipolar disorder which has not been diagnosed by the primary clinical team but detected at baseline in the course of the research will not be excluded because in NHS clinical practice they would be looked after by specialist depression disorders and usual care teams.

### Interventions

#### Specialist Depression Disorder Team (SDDT)

The SDDT will consist of a team of psychiatrists and cognitive behaviour therapists who will work together. All of them are experienced clinicians who treat depression as part of the secondary health care service. They will take a stepped care approach as outlined by the NICE guidelines. A key feature of the specialist mood disorder team is that a psychiatrist and a cognitive behaviour therapist will jointly assess the patient and agree upon a joint formulation of the patient's problems focusing on maintaining factors for the depression. They will then agree upon a joint management plan and review progress during treatment so that the two management approaches complement each other. The psychiatrist will follow a treatment algorithm derived from NICE guidelines for drug treatment of depression, British Association of Psychopharmacology [13] and findings from the STAR*D project [9] after an assessment and review of recent treatment (copy available from the authors). This treatment algorithm is a guide to be interpreted in the light of the assessment made by the psychiatrist and the patient's treatment history. All participants in the intervention group will receive at least a psychoeducation approach incorporating cognitive behaviour therapy (CBT) techniques. However, some patients will receive mindfulness based CBT [25], standard CBT [26] or compassionate mind based CBT [27] according to the therapist's assessment. The psychiatrist and cognitive behaviour therapist will also consider social approaches and when relevant consult professionals providing social care to complement pharmacological and psychological interventions. Physical treatments such as electroconvulsive therapy will not be employed by the SDDT.

Participants being treated by the SDDT will each receive a unique treatment plan tailored to their specific needs. They may receive up to three or four different drug treatment approaches and two different psychological treatment approaches over the 12 month intervention period. The nature, time taken, form and content of the assessments, supervision, decisions and discussions between different members of the specialist depression disorder team will be logged and recorded.

At the end of the study participants will be re-integrated into their usual care team. Any new medications started will be continued with usual care but any psychological treatment will be completed.

#### Treatment as usual

Treatment as usual will be provided by the clinical team that referred the patient to the study and will be unconstrained other than it will not be provided by the psychiatrists in the SDDT. Economic data collection and an audit of case notes will provide information on the interventions given during treatment as usual within the trial itself.

### Outcomes

**Primary outcome **measures are:

1. Longitudinal change in the 17-item observer rated Hamilton Depression Rating Scale (HDRS) [23,28] from baseline to 6 and 12 months as well as follow up assessments at 18 and 24 months. The primary analysis will be change over the baseline to 6 and 12 months. The purpose of the analysis at 18 and 24 months is to determine if any change is maintained once the patient has been discharged from the specialist depression disorder team.

2. Change in global assessment of function [24] from baseline to 6 and 12 months as well as follow up assessments at 18 and 24 months.

**Secondary outcome **MEASURES ARE:

1. Change in self-rated depression: a) self-rated Beck Depression Inventory version 1 [29], a measure of cognitive symptoms of depression from baseline to 3, 6, 9, 12, 18 and 24 months; b) Personal Health Questionnaire [30] from baseline to 3, 6, 9, 12, 18 and 24 months, rating of depression severity according to DSM-IV criteria; c) Quick Inventory for Depressive Symptomatology self rated version [31] from 3, 6, 9, 12, 18 and 24 months, a 16-item screening/diagnostic questionnaire rating depression severity according to DSM-IV criteria. The last scale has the best established psychometric data for remission compared to the Hamilton Depression Rating Scale. The other two scales are widely used in clinical practice by general practitioners and psychotherapy services in England and Wales.

2. Euroqol 5 D [32] as a measure of quality of life and costs from health and social care and society perspectives measured at 6, 12, 18 and 24 months. Use of the EQ5 D will enable utility score sto be gained from the patients that may then be used in a cost utility analysis

3. Change in social adjustment [33], an assessment of social and occupational functioning from baseline to 6, 12, 18 and 24 months.

4. Patient satisfaction and relationship with the clinician(s) on a four part 9-item questionnaire based on two other questionnaires used frequently in depression studies: the Patient Satisfaction Questionnaire [34] and the Patient Doctor Relationship Questionnaire [35]. These will be measured at 6, 12, 18 and 24 months.

**Process measures**, which will not be utilised to determine the effectiveness of the interventions, but will be used to understand the processes that are taking place:

1. At baseline care received will be audited against standards of care outlined in NICE Guidelines [8,20] according to a 4-point scale (1 = not followed NICE Guideline, 2 = followed NICE Guideline< 50% of the time, 3 = followed NICE Guideline > 50% of the time, 4 = fully followed NICE Guideline) by an independent clinical expert. This assessment will then be applied to each three month block of care during the 12 month follow-up.

2. The number of patients with unrecognised axis 1 and 2 psychopathology [24] and medical co-morbidity will be recorded by the research team and also audited against treatment notes to determine if the specialist team is more accurate in terms of diagnosis.

3. At baseline life events and difficulties in the preceding 6 months and at 6, 12, 18 and 24 months after baseline will be recorded using the Brugha 12-item life event checklist [36]. The recognition or not of these life events and difficulties according to case notes will be audited in the two treatment groups.

4. At baseline social support in the preceding 6 months and at 6, 12, 18 and 24 months after baseline will be recorded using the 3 item social support and social network measure [37], which examines such support networks. The recognition or not of this social support according to case notes will be audited in the two treatment groups.

5. Adherence to medication [38], assessed at 6 and 12 months.

Quality of relationship between the patient and any secondary care mental health professional they have seen on a planned ongoing basis to manage their depression on a 9 item patient rated scale [35] assessed at baseline, 6 and 12 months.

6. Brief self-rated measures demonstrating the suitability of the cognitive therapy offered to the patient's needs: a) 18-item Others as Shamer Scale [39]; b) 22-item Forms of Self-criticising/attacking and Self-reassuring Scale [40]; c) 26-item How I act towards myself in difficult times scale [41]; d) 16-item Social Comparison Scale [42]; e) 16-item Entrapment Scale [43]; f) 16-item Defeat Scale [43]; g) 39-item 5 Facet Mindfulness Questionnaire [44].

7. At baseline, 6, 12, 18 and 24 months, participants' overall ruminative processes will be captured using the Rumination Scale [45]. Symptoms of rumination can predict vulnerability to depression, particularly relapse. As psychological treatments in the specialist mood team will aim to modify the ruminative process, this questionnaire will inform us whether this aim is being achieved.

8. At baseline, 6, 12, 18 and 24 months, participants' overall tendencies to avoid thinking about painful emotional issues will be measured using The Acceptance and Action Questionnaire-1 [46]. Patients who score highly on this measure are likely to need more preparation before they can undertake psychological treatment.

All measures will be assessed at baseline, 6, 12, 18 and 24 months face-to-face by the research associate (unless otherwise stated). At 3 and 9 months the Beck Depression Inventory, the PHQ-9, the QIDS-SR and a questionnaire version of the health economics interview will be mailed to all participants.

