### Sample size and justification

Sample size calculation was based on improvement in global assessment of severity in a study using a similar design, except that it employed a mixed diagnostic group rather than moderate to severe primary depressive disorder [14], 90% power, 2 tailed difference at 5% significance, 20% loss to follow up was 52 per treatment group (104 in total). However, this study did not employ an intention to treat analysis and there was a 30 percent loss to follow-up; therefore, the sample size has been inflated by a further 43 percent to 74 per group (148 in total). A further correction is to be made for the variability in the individual treatment from the SDDT and treatment as usual. A multiplicative correction factor to the sample size estimate of 1.18 calculated from [1 +rho*r/(1-rho)] [48] where rho is the intraclass correlation of 0.051[49] and r is the number of patients from each community mental health team (CMHT) per treatment arm (3-4). Therefore, the sample size is 87 per treatment group (174 in total). Sample size calculations were checked against a study of in-patient delivered combined psychotherapy and pharmacotherapy versus treatment as usual for patients with chronic depressive disorder [15]. The primary outcome variable was the 17-item Hamilton Depression Rating Scale (HDRS) and patients were followed up for 12 months. At baseline the combined treatment mean (sd) HDRS was 25.6 (4.4) and for clinical management it was 23.5 (4.8). At 12 months the HDRS score was 5.9 (5.1) in the combined treatment group and 11.3 (10.5) in the clinical management group (intention to treat analysis). Using a 2-tailed students t-test, 90% chance of detecting a difference at 0.05 level, and an effect size of 0.65, 51 patients per group are required (102 in total). If a 20 percent drop-out is assumed, then 122 patients (61 in each group) are required. Using the correction factor of 1.18 previously justified results in a sample size of 146 (73 in each group). In line with the more conservative estimate of the power of the study our aim is to recruit 87 patients per treatment group (174 in total).

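### Process measure 2 names only a count of missed diagnoses, yet uses it to judge whether the specialist team diagnoses more accurately

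*Protocol article*

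**What the plan says.** The Outcomes section of the protocol article introduces a set of process measures and limits their role: "which will not be utilised to determine the effectiveness of the interventions, but will be used to understand the processes that are taking place". The second reads: "The number of patients with unrecognised axis 1 and 2 psychopathology [24] and medical co-morbidity will be recorded by the research team". The same sentence adds that this is "audited against treatment notes to determine if the specialist team is more accurate in terms of diagnosis".

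That is all the article says about the measure. It does not mention diagnoses in the notes that the research assessment fails to support, nor specificity or agreement.

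Three other places bear on it:

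- **Sample and inclusion/exclusion criteria** names a structured interview for Axis 1: "The Structured Clinical Interview for DSM-IV Axis 1 Disorders [21] will be used to describe patients' symptom profile at baseline".
- **Outcomes, process measures 3 and 4** (life events, social support) also audit the case notes in both arms, but claim only to show whether these were recognised. Measure 2 alone moves from recognition to accuracy.
- **Objectives, item 2** seeks the important constituents of effective care, and process findings of this kind would inform it.

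**The concern.** Diagnostic accuracy has two components: finding disorder that is present, and not recording disorder that is absent. A count of unrecognised disorder sees only the first. Adding a diagnosis to the notes, right or wrong, can lower the count or leave it unchanged, but can never raise it. A team with a low threshold for diagnosis therefore gains on this measure and loses nothing for its errors.

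At stake is one stated conclusion. The trial could report that the specialist depression disorder team (SDDT) diagnoses more accurately than usual care when it has shown only that fewer disorders were missed. That could then be presented as one of the ingredients that make the service work.

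**Working it through.** **Plan's own figure.** There is none. The article gives no prevalence, sensitivity, specificity, agreement target or power for this measure, and the sample size does not rest on it. Every value below except the arm size is an assumption.

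**Formulas.** For *n* patients, prevalence *p*, sensitivity *Se* and specificity *Sp*:

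- missed (the count named in the plan) = *n* × *p* × (1 − *Se*)
- recorded but not present = *n* × (1 − *p*) × (1 − *Sp*)
- accuracy = 1 − (missed + recorded but not present) / *n*

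*Sp* does not appear in the first line, so the named count carries no information about over-diagnosis.

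**Illustration 1**, as a share of patients. Assume *p* = 0.30; usual care *Se* 0.60, *Sp* 0.95; SDDT *Se* 0.80, *Sp* 0.80.

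- Missed: usual care 0.30 × 0.40 = 12%; SDDT 0.30 × 0.20 = 6%.
- Recorded but not present: usual care 0.70 × 0.05 = 3.5%; SDDT 0.70 × 0.20 = 14%.
- Total errors: 15.5% against 20%.

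The count halves while total errors rise. The two teams have equal total errors when 0.06 + 0.70 × (1 − *Sp*) = 0.155, which gives *Sp* = 1 − 0.095/0.70 = 0.864. Above about 86%, the SDDT has fewer total errors and the count ranks the arms correctly.

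**Illustration 2**, with 87 per arm (the target in Sample size and justification) and a range of prevalence. Assume usual care *Se* 0.50, *Sp* 0.95; SDDT *Se* 0.80 with *Sp* either 0.60 or 0.85.

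| Prevalence | Team | Missed | Recorded, not present | Total errors | Accuracy |
|---|---|---|---|---|---|
| 20% | Usual care | 8.7 | 3.5 | 12.2 | 86% |
| 20% | SDDT, *Sp* 0.60 | 3.5 | 27.8 | 31.3 | 64% |
| 20% | SDDT, *Sp* 0.85 | 3.5 | 10.4 | 13.9 | 84% |
| 30% | Usual care | 13.0 | 3.0 | 16.1 | 81.5% |
| 30% | SDDT, *Sp* 0.60 | 5.2 | 24.4 | 29.6 | 66% |
| 30% | SDDT, *Sp* 0.85 | 5.2 | 9.1 | 14.4 | 83.5% |
| 50% | Usual care | 21.8 | 2.2 | 23.9 | 72.5% |
| 50% | SDDT, *Sp* 0.60 | 8.7 | 17.4 | 26.1 | 70% |
| 50% | SDDT, *Sp* 0.85 | 8.7 | 6.5 | 15.2 | 82.5% |

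At each prevalence the two SDDT rows have the same missed count, 60% below usual care. With *Sp* 0.60 the SDDT is less accurate throughout. With *Sp* 0.85 it is slightly less accurate at 20% prevalence and more accurate at 30% and 50%. The count cannot tell these cases apart. In the limit, a team that labels every patient has no missed cases, and its accuracy equals the prevalence.

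**Choice of summary.** Youden's index (*Se* + *Sp* − 1) in Illustration 1 is 0.55 for usual care and 0.60 for the SDDT, so on that summary the ranking does not reverse. In Illustration 2 with *Sp* 0.60 it is 0.45 against 0.40, and it does. This is a reason to report both kinds of error rather than one number.

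**The case against.** The strongest reply is that the article provides for an audit of the treatment notes and does not say what it will tabulate. The audit could pick up diagnoses that the research assessment does not confirm, and a condensed article may leave such detail to the full protocol. This stands in part: a reader might infer that unconfirmed diagnoses will never be counted, and the text does not establish that. But the article does commit itself to one quantity and one inference, and the first cannot carry the second.

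The reply that this is a process measure, barred from determining effectiveness, also stands, and it limits the consequence. A reader might infer a route into the main results, because the Statistical analysis section uses first-stage process findings to look for covariates. Nothing there says this count would be selected, so that is not claimed.

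Three further inferences are tempting and unsupported:

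- **That Axis 2 disorder has no reference standard.** The article names no instrument, but it attaches a citation and may leave the instrument to the full protocol.
- **That the SDDT's activity log inflates its recorded diagnoses.** The log is described under Interventions; the audit uses treatment notes, and nothing says that the log enters it.
- **That barring outcome assessors from health records removes an independent standard.** Under Randomisation, the bar applies to those assessors, not to whoever audits the notes. It would tend to keep the research assessment independent of them.

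Finally, no passage suggests that joint assessment lowers specificity. The reversal needs an assumed loss of specificity, about 8.6 points in Illustration 1 (0.95 to 0.864).

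**Conclusion.** The point holds in a limited form. The measure as stated supports a conclusion about recognition of disorder, not about diagnostic accuracy. A freer-diagnosing team could appear more accurate when it is not. This is a possibility, not a prediction: under the assumed values the ranking by total errors reverses in some scenarios and not in others, and the named count looks the same in both.

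The effect is confined to one process conclusion and its use under objective 2. The primary outcome and the sample size are untouched. The correction is still worth making, because it changes what the trial may claim about the specialist team and costs little.

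**What to change.** Either of two changes is enough.

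1. **Keep the accuracy claim and measure it.** In the planned notes audit, also count Axis 1 diagnoses in the treatment notes that the baseline structured interview does not confirm. Limit this to disorders recorded as present around trial entry, so that a disorder arising later is not scored as an error. State that the baseline interview is the reference for this comparison, since the article gives its purpose only as describing symptoms. Compare the arms on both missed and unconfirmed diagnoses, by sensitivity and specificity or by kappa.
2. **Keep the count and narrow the claim.** Replace the statement about accuracy with one about recognition of disorder, in line with process measures 3 and 4.

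The first costs one more column in an audit already planned and a two-by-two table per disorder. The second costs only a change of wording and a narrower conclusion.
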